## Methods and design

This study is a dual-centre, randomised controlled trial with blinded assessors. Participants (*N* = 240) were randomly assigned to one of two groups (multifactorial intervention or usual care control group) in a 1:1 ratio after initial assessment (−T1) and before discharge from inpatient rehabilitation. Computer-generated random allocation was done by an independent randomisation centre (University of Ulm) and sealed envelopes are used. The randomisation of participants was conducted by the interventionists. The study design is outlined in Fig. 1*.*

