#### Interventionists

The exercise instructors in *Module 1* are physiotherapists and sports scientists, called exercise instructors, who are experienced in rehabilitation of cognitively impaired older adults. After an initial training, they are supervised by a clinical psychologist (KP) or a senior sports scientist (KH) both with long-standing experience in fall prevention, exercise programs and rehabilitation.

The interventionists in *Module 2* are a social worker and a gerontologist both highly experienced in counselling for older adults and family caregivers. Like the therapists in *Module 1* they received an initial training and are supervised by clinical psychologists (KP, MS) during the intervention period of the study.

The lay instructors have been recruited from different sources (visitor services for people with dementia, sports clubs, municipal elderly council, local newspapers, churches, public lectures on physical activity in older age). For their engagement, they get expense allowances according to the standards of local visitor services at the two recruitment sites. Before participating in the intervention, they are trained in two 4-h group sessions with a maximum of 12 participants. Every course is held together by an exercise instructor and a gerontologist. The components of the intervention delivered by the lay instructors are presented in lectures and exercises. Key elements are the exercise protocol, basic understanding about training control and progression, motivational aspects, use of walking aids, safety issues during exercising, medical or emotional exercise termination criteria and important aspects in the interaction with cognitively impaired persons.

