### Sample size

For sample size calculation, a two-step method was used. First, the sample size (N) was calculated as if a t-test on the T2 scores will be carried out, then the number of subjects was multiplied by a “design factor: (1 - ρ^2^)*N” (ρ = correlation between the outcome measured at baseline and at follow-up) to produce the number of subjects required for calculating an ANCOVA [84].

The estimated effect size calculation is based on the measured daily walking time (activPAL™) in a previous hip and pelvic-fracture study (ISRCTN79191813) as well as on the following assumptions: (a) daily mean walking time (completer, control condition with standard care) at discharge (M = 35.5 Min, SD = 27.9 Min); (b) daily walking time on average four months post-discharge from rehabilitation (M = 44.9 Min, SD = 34.8 Min); (c) a correlation of ρ = 0.45 between baseline and follow-up data; (d) an intended significant improvement of daily walking time of 30% (13.5 Min) which corresponds to an effect size Cohen’s d = 0.39; (e) β = .80 (power) and (f) α = .05 for two-sided testing.

The required number of cases for a two-sided t-test for independent samples is 106 persons in intervention and control group respectively (G*Power 3.1.9.2 [85]). The adjusted number of cases for the ANCOVA with the same power as for the t-test results in 85 persons per group [design factor: (1–0.45^2^)*106].

Using the data of the previous study in the same way for the SPPB, the design factor for this other primary outcome is lower (1–.64^2^). This means that with a sample size of 85 per group smaller effects for SPPB can be detected (Cohen’s d = 0.33) compared to the daily walking time (Cohen’s d = 0.39). Based on previous studies with hip or pelvic fracture patients a drop-out rate of 22.5% until T3 is expected. Therefore, the adjusted required number of cases is calculated with 110 patients in each group.

At the time of finalizing the study protocol for publication, an adjustment of the required sample size had been made (120 participants in each group) due to a higher drop-out rate than assumed before. Several participants had to be excluded because they went to short-term care after discharge from rehabilitation and could not return home later on.

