### Data analyses

Descriptive analyses will be carried out to present baseline characteristics of both groups. Treatment effects on primary and secondary endpoints at T2 (after intervention) and T3 (at follow-up) will be analysed with analyses of covariance (ANCOVA), using baseline scores at t_1_ as covariates. In addition to intent-to-treat and completer analyses, subgroup analyses are planned (participants with pelvic fracture, MMSE total scores < 24, fear of falling, significant depressive symptoms). Since intent-to-treat analyses may underestimate active intervention components, the conduction of additional analyses (e.g. complier average causal effect) depending on type, randomness and degree of non-compliance is planned [86].

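### The ANCOVA and the sample size make no allowance for instructors and counsellors shared in the intervention arm only, so precision and power may be overstated by an amount the article cannot settle

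*Protocol article*

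**What the plan says.** Treatment effects at T2 and T3 are to be analysed by ANCOVA, "using baseline scores at t_1_ as covariates" (Data analyses). The T1 score is the only covariate named; neither centre nor provider appears.

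Methods and design states: "This study is a dual-centre, randomised controlled trial with blinded assessors". Individual patients "were randomly assigned to one of two groups (multifactorial intervention or usual care control group) in a 1:1 ratio". Stratification by centre is not mentioned.

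The Sample size section starts from an independent-samples t-test with "β = .80 (power) and (f) α = .05 for two-sided testing" and applies the usual ANCOVA reduction. The later increase to 120 per group is attributed to drop-out. No design effect appears.

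Delivery is described under Intervention and Interventionists:
- The exercise instructors are physiotherapists and sports scientists, number not given.
- The lay instructors come from several sources, number not given. Table 2 has them conduct 32 of the 35 supervised sessions without a professional.
- Module 2 is delivered by "a social worker and a gerontologist both highly experienced in counselling for older adults and family caregivers".
- The control group has usual care and no study instructor or counsellor.

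**The concern.** Patients treated by the same person may have correlated outcomes, through the provider's skill, rapport or way of progressing the exercises. Here the content is individually tailored, part of each lay visit is unstandardised, and Module 2 fixes only a minimum of contacts, so provider effects are plausible. They would arise in one arm only.

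An ANCOVA that treats all patients as independent then uses too small a variance for the intervention-arm mean. A borderline primary result could cross the 5% threshold because of that, and the trial would have less power than stated. The planned power leaves almost no slack to absorb this.

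**Working it through.** **The plan's own figures.** Inputs from the Sample size section are "M = 44.9 Min, SD = 34.8 Min" at follow-up, a difference of 13.5 min, a correlation of 0.45 and 22.5% drop-out.

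- Effect size: 13.5/34.8 = 0.388, stated as 0.39.
- Two-sided t-test, α 0.05, power 0.80, d = 0.388: 106 per group, as stated.
- ANCOVA: (1 − 0.45²) × 106 = 0.7975 × 106 = 84.5, so 85, as stated.
- Drop-out: 85/0.775 = 109.7, so 110, as stated.
- Power at 85 analysed per arm, d = 0.39, normal approximation: the adjusted standard error is √0.7975 × √(2/85) = 0.893 × 0.1534 = 0.137. Then 0.39/0.137 = 2.85 and Φ(2.85 − 1.96) = 0.81.
- The move to 120 per group preserves 85 analysed if drop-out is 1 − 85/120 = 29%. It answers attrition and does not allow for clustering.

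The arithmetic is sound if patients are independent.

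**Allowing for shared providers in one arm.** Assumptions not in the article: m analysed patients per provider, ICC from 0.01 to 0.05, equal total variance in both arms, and providers regarded as a random sample. With 85 analysed in the intervention arm, m = 8 to 21 means roughly 11 down to 4 exercise instructors. For the two counsellors, m = 85/2 = 42.5.

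- Intervention-arm design effect: DE = 1 + (m − 1) × ICC; control arm DE = 1.
- Variance ratio of the difference: f = (DE + 1)/2; true SE / model SE = √f.
- Type I error of the unadjusted test: 2 × [1 − Φ(1.96/√f)].
- Power of a test using the correct standard error: Φ(2.85/√f − 1.96).
- Analysed per arm needed: 85 × f, rounded up.

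Example, m = 21 and ICC 0.05: DE = 1 + 20 × 0.05 = 2.0; f = 1.5; √f = 1.225. Type I error = 2 × [1 − Φ(1.600)] = 0.1095. Power = Φ(2.32 − 1.96) = 0.64. Needed: 127.5, so 128.

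| Provider level | m | ICC | DE | SE ratio | Type I error | Power | n per arm |
|---|---|---|---|---|---|---|---|
| None | – | 0 | 1 | 1 | 0.0500 | 0.812 | 85 |
| Lay instructor | 2 | 0.01 | 1.010 | 1.002 | 0.0506 | 0.811 | 86 |
| Lay instructor | 4 | 0.05 | 1.150 | 1.037 | 0.0587 | 0.784 | 92 |
| Exercise instructor | 8 | 0.01 | 1.070 | 1.017 | 0.0540 | 0.799 | 88 |
| Exercise instructor | 15 | 0.02 | 1.280 | 1.068 | 0.0664 | 0.760 | 97 |
| Exercise instructor | 21 | 0.05 | 2.000 | 1.225 | 0.1095 | 0.642 | 128 |
| Counsellor | 42.5 | 0.01 | 1.415 | 1.099 | 0.0745 | 0.736 | 103 |
| Counsellor | 42.5 | 0.05 | 3.075 | 1.427 | 0.1697 | 0.514 | 174 |

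**Simulation check.** The baseline-only ANCOVA was fitted to data with no average treatment effect, 85 per arm, 8,000 runs (simulation standard error about 0.24 percentage points). At ICC 0.02 its type I error was 5.2% with 40 providers, 6.4% with 8, 7.6% with 4 and 9.8% with 2. This agrees with the formula.

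**Centre.** A second simulation (84 per arm, two equal centres, no treatment effect) left centre out of the model. For centre differences of 0.3 and 0.6 SD, type I error was 4.4% and 5.3% with unstratified randomisation, and 4.5% and 4.0% with randomisation stratified by centre. None exceeds 5% beyond simulation error.

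**The case against.** The strongest reply has four parts.

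- **A condensed article.** Naming one covariate does not exclude others, and random effects or a centre term are usual content of an analysis plan that is not shown. This stands: a reader might infer that the analysis adjusts for nothing else, and the article does not say so. It does not dispose of the point, because the sample size is set out in full, assumes independence, and cannot be altered by a later analysis plan.
- **Assumed inputs.** No caseload and no ICC is stated, and only the counsellors are counted. This stands too. The larger figures belong to exercise instructors, who by Table 2 attend only 3 of the 35 supervised sessions, although they also choose the exercises and supervise the lay instructors. For lay instructors, who have most of the contact, the effect nearly vanishes if each has 2 to 4 patients.
- **The inference target.** If the intervention did nothing for anyone, who delivered it could not matter, and the ANCOVA would keep its 5%. Inflation needs provider effects that vary around a zero average, with these providers standing for a wider population. That is a choice, though a reasonable one, since the Discussion plans wider implementation.
- **Recruitment.** Eligibility assessment ended in February 2018, so the sample size is settled. This is correct; what can still change is the analysis and how the power is described.

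A reader might also infer that leaving out centre makes standard errors too small. The design does not support that: patients are individually randomised, so centre is not confounded with arm as provider is. Leaving it out puts the centre difference into the residual, which costs precision and is conservative if randomisation was stratified.

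**Conclusion.** The point holds as a limited one. The stated model and sample size make no allowance for providers shared in the intervention arm only, so the standard error can be too small, and the 80% power holds only without provider clustering.

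Within the assumed ICC range, the effect runs from near negligible (lay instructors) to possibly material (exercise instructors). The counsellor figures are larger still, but two clusters do not allow that variance to be estimated reliably, so they mark a limitation and not a measured error.

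The documents do not support saying that the true type I error is 11% or that the trial is underpowered; both need caseloads and ICCs that are not given. Nor do they justify replacing the primary ANCOVA, since the relevant cluster level is itself open. Centre is a matter of precision only.

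**What to change.** Before the outcome data are analysed:

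1. Add centre as a fixed covariate to the ANCOVA models for primary and secondary endpoints.
2. Keep the ANCOVA as the primary analysis. Pre-specify a partially nested mixed model as a sensitivity analysis for daily walking duration and the SPPB: a random intercept for exercise instructor in the intervention arm only, arm-specific residual variance, and small-sample degrees of freedom. Fit it separately with lay instructor as the cluster.
3. Report the number of instructors, their caseloads and the estimated ICC.
4. State that the 80% power assumes no provider clustering.
5. Acknowledge that clustering by the two counsellors cannot be modelled.

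The cost is one degree of freedom for centre, some extra analysis, and possibly wider intervals in the sensitivity analysis: up to about 22% wider in the m = 21, ICC 0.05 case, before the degrees-of-freedom correction. No new data collection should be needed, because interventionists and lay instructors already record their visits (Adherence to intervention protocol). If the instructor variance is estimated as zero, the result will be close to the ANCOVA but not identical, because the residual variances and degrees of freedom differ.

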Although, there is no gold standard intervention for improving mobility after hip fracture [17], structured exercises with appropriate progression and intensity have been found to be effective [18, 19]. While supervised exercise regimes can be implemented easily during inpatient rehabilitation, the continuation of regular, progressive and enjoyable exercise regimes after discharge is challenging. Many people, in particular those with cognitive impairment may prefer to exercise at home rather than attending group sessions. While home based exercise interventions with cognitive behavioural components and minimal supervision can improve physical performance of hip fracture patients without cognitive impairment [20], there is only little evidence derived from subgroup analyses or non-randomised studies for cognitively impaired hip fracture patients. These previous results support that rehabilitation appears to be beneficial for this subgroup, in particular if it is tailored to preferences of the patients in interdisciplinary approaches [21]. However, specific interventions for cognitively impaired patients in the transition from hospital to home which address mobility issues and the need for added support and resources (also for their caregivers) are missing from the literature so far [22].

In contrast to current intervention research for hip fracture patients, comparable research for pelvic fracture patients is lacking. Despite the differences in the (non-) operative treatment of the different fracture types, it is assumed that in early discharge and community rehabilitation both patient groups can be addressed with the same intervention approach.

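### Subgroups are named as one-sided subsets with no comparison against their complements, so a pelvic-only result would say little about whether the effect differs from hip fracture (minor point)

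*Protocol article*

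**What the plan says.** All references are to the protocol article.

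- **Data analyses.** Effects at T2 and T3 on primary and secondary endpoints are analysed by ANCOVA, "using baseline scores at t_1_ as covariates". Beyond the intent-to-treat and completer analyses, "subgroup analyses are planned (participants with pelvic fracture, MMSE total scores" below 24, fear of falling and significant depressive symptoms. The section mentions no complement, contrast or interaction term, and it does not rule one out.
- **Background.** After noting that comparable intervention research in pelvic fracture is lacking, the authors write that "it is assumed that in early discharge and community rehabilitation both patient groups can be addressed with the same intervention approach".
- **Methods and design.** "This study is a dual-centre, randomised controlled trial with blinded assessors". Allocation is 1:1, and no stratification factor is stated.
- **Sample size.** The target is "an intended significant improvement of daily walking time of 30% (13.5 Min) which corresponds to an effect size Cohen’s d = 0.39", with "α = .05 for two-sided testing".

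**The concern.** The list describes sets of patients to be analysed, not factors whose levels are to be compared. Its plainest reading is one ANCOVA within each set. A p-value from a small subset shows neither that an effect is absent there nor that it differs from the effect elsewhere.

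This matters most for pelvic fracture. Enrolling both fracture types rests on the premise that one programme suits both, and the pelvic subset is the first one named. A non-significant pelvic result could be taken to mean that the programme fails in those patients. Conversely, one significant subset among four could be presented as a finding. Only a contrast of the treatment effect between pelvic and hip fracture bears on whether the effect differs.

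**Working it through.** **Inputs from Sample size:** effect 13.5 min/day, SD 34.8 min at about four months, correlation 0.45, two-sided alpha 0.05, power 0.80, drop-out 22.5%.

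**Assumption:** the pelvic share is not in the article, so 10% to 50% of the analysed patients is used.

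**1. The plan's own figures reproduce.**
- d = 13.5 / 34.8 = 0.388. The t-test solution is 105.3, so 106 per arm.
- ANCOVA: 106 × (1 − 0.45²) = 84.5, so 85 per arm (170 analysed).
- Drop-out: 85 / (1 − 0.225) = 109.7, so 110 per arm.

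**2. Residual SD after baseline adjustment.** 34.8 × √(1 − 0.45²) = 31.08 min. With 85 per arm, overall power is 80.8%.

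**3. Test inside the pelvic subset, n patients per arm.** SE = 31.08 × √(2/n); power = Φ(13.5/SE − 1.96) (normal approximation; the opposite tail is negligible). For a 20% share, n = 17, SE = 10.66 and power = Φ(1.27 − 1.96) = 24%. A t-based calculation gives 23%.

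**4. Treatment-by-fracture interaction.** SE = 31.08 × √(2/n_pelvic + 2/n_hip), with n per arm. For a 20% share this is 31.08 × √(2/17 + 2/68) = 11.92. Power for a 13.5 min difference in effect is 21%, and the difference detectable with 80% power is (1.96 + 0.84) × 11.92 ≈ 33.4 min.

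| Assumed pelvic share | Pelvic n per arm | Power, pelvic-only test, 13.5 min | Power, interaction, 13.5 min difference | Difference detectable with 80% power |
|---|---|---|---|---|
| 10% | 8.5 | 14% | 14% | 44.5 min |
| 20% | 17 | 24% | 21% | 33.4 min |
| 30% | 25.5 | 34% | 25% | 29.1 min |
| 50% | 42.5 | 52% | 29% | 26.7 min |

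**5. What a non-significant pelvic result would tell us.** If the full effect were present in pelvic fracture, the pelvic-only test would still miss it in 48% to 86% of trials (1 − 0.52 to 1 − 0.14). At a 20% share the miss rate is 76%, against 95% if there were no effect at all. The ratio is 0.95 / 0.76 = 1.25, so the result hardly separates the two cases.

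**6. Chance findings.** With no true effect, four independent tests give 1 − 0.95⁴ = 18.5% for at least one significant subset, for one outcome at one visit. The subsets overlap, so this is approximate.

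**7. Extra covariates.** If site and fracture type explained an assumed further 1%, 2% or 5% of residual variance, overall power would move from 80.8% to 81.2%, 81.6% or 82.8%.

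**The case against.** The strongest reply is that the article is a condensed account. Naming the group of interest is ordinary shorthand for a subgroup factor, and model detail normally sits in an analysis plan, which is not shown. This stands in part. A reader might infer that the trial has decided against interaction tests; the text does not say so. What remains is that the article itself chose to publish the subgroups in one-sided form, and that this form, followed literally, leads to the weak analysis.

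A second reply is that the shared-programme premise is background rationale and not one of the listed objectives. That is correct, and the trial is not obliged to test it. But a pelvic subgroup is planned, and its result should be produced in a form that can be interpreted.

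A third reply is that the interaction is no better powered. This also stands: 14% to 29%, against 14% to 52% for the subset test. The case for the interaction is that it addresses the right question and shows its uncertainty, not that it would settle the matter.

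A reader might also infer that leaving site and fracture type out of the ANCOVA is an error, or is why the premise goes untested. Neither follows. Omitting prognostic covariates does not bias a randomised comparison, and no stratification factor is stated whose adjustment could be missing. Fracture type as a main effect would not test whether the treatment effect differs, and site has no bearing on that question.

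**Conclusion.** The point holds as a minor one about supplementary analyses. As written, the subgroups are one-sided subsets without comparison to their complements. For pelvic fracture, such an analysis has roughly 14% to 52% power for the planned effect and cannot show a difference from hip fracture. These figures rest on 170 analysed patients, the stated SD and correlation applying equally in both fracture groups, and an assumed pelvic share of 10% to 50%. The conclusion is the same across that range. The interaction is the appropriate estimate, but at this size it is imprecise: only differences of about 27 to 45 min, two to 3.3 times the planned effect, would be detected with 80% power. The primary analysis and the sample size are not called into question.

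**What to change.** State in Data analyses that subgroup effects will be estimated from treatment-by-factor interactions in the full-sample ANCOVA, for fracture type (pelvic versus hip), MMSE (below 24 versus 24 to 26, given the 17 to 26 entry range), fear of falling and depressive symptoms. Report the effect in both strata and the difference between them, each with a 95% confidence interval. Label these results exploratory, and say that a non-significant interaction will not be taken as evidence of equal effects. If an analysis plan already provides for this, one sentence pointing to it is enough.

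Optionally, add site, fracture type and baseline MMSE as covariates in the primary model. For site and fracture type the gain is about 0.4 to 2 points of power under the assumption above; no figure was worked out for MMSE. It is a small matter of precision, not a correction.

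The cost is wording only: no new data, no extra patients, and a few degrees of freedom out of about 170.

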## Discussion

The aging society with an increasing number of osteoporotic fractures requires effective, sustainable and economic rehabilitation regimes to limit rising costs for long-term care [1, 7, 87]. The need for a tailored rehabilitation approach to regain maximum functional independence is even more pronounced in hip and pelvic fracture patients with cognitive impairment [22]. The idea of this home-based intervention was to develop and evaluate a set of actions designed to ensure a better continuity and coordination of care after inpatient rehabilitation. Our main aim of this transitional care approach was to promote physical activity and to ensure regular exercising with appropriate intensity and continuous supervision *(Module 1)*. It has been shown that a moderate frequency of supervised home-based exercises ensures good adherence and thus improves program efficacy in frail older people [88]. The training is embedded in home visits of the lay instructor in which further valued psychosocial aspects can be addressed for most of the patients. It is assumed that this kind of reinforcement will have an additional positive effect on the acceptance and adherence of the training.

Furthermore, it is tried to ensure that the patients receive the necessary and available support to remain living in their own homes. Based on individual goals, preferences and health status, problem-solving coping is supported, and education of patient and caregiver, as well as coordination among health professionals is provided *(Module 2)*. The demand for support will differ in this target group due to the patients´ high variety of physical and cognitive capacity. Therefore, just a minimum of contacts has been standardized in the intervention protocol in this module.

To increase the likelihood of a future implementation into services the study protocol has been developed based on visit frequencies and expense allowances of existing visitor services for Alzheimer patients and the statutory care counselling according to the national social legislation (social act/ §7a SGB XI) (*Module 2*). The inclusion of professionals, lay instructors, and caregivers is in accordance with the principle of subsidiarity that should be further strengthened by favourable conditions, local structures and reimbursement models. For implementing the intervention, it must be ensured that the lay instructors are trained and supervised adequately to consider safety and security aspects (e.g. mistreatment, abuse), to avoid physical and mental overload of the cognitively impaired patients as well as of the lay instructors themselves. Further, the lay instructors should be aware of the limits of their provided non-professional assistance. The limited set of self-exercises for the unsupervised training is selected due to security aspects and can have a too low intensity for some patients.

So far, in Germany, a standardized coordination of transitional care between health professionals of rehabilitation departments, community physiotherapy and long-term care counselling does not exist for this vulnerable target group. It is expected that a shared systematic assessment of patient’s goals in combination with regular strength and balance exercises improve or at least stabilize rehabilitation outcomes.

To the authors´ knowledge this is the first study to examine the effects of a multifactorial home-based, lay-led exercise intervention combined with long-term care counselling in cognitively impaired individuals after hip and pelvic fracture. Based on the results of this study, a future translation and implementation of the intervention in collaboration with health care insurances, visitor services, and local care counselling centres is planned.

